## 10. STATISTICAL ANALYSIS

Statistical Data analysis of the study data will be performed using SPSS (version 17.0). All analyses will be performed through Intention to treat.

### 10.1 Primary study parameter

The primary outcome is defined as being attack free at 12 months follow-up. The required significance level of findings ( $\alpha$ ) will be equal to or lower than 5%. Any statistical tests will be two-sided. P-values will be presented. Where confidence limits can be estimated, the confidence level will be 95%. All analyses will be performed by intention to treat.

A chi-square test (or Fisher's exact test) will be performed on the primary outcome variable data (number of patients free of vertigo attacks at 12 months post-operatively, in EDB vs endolymphatic sac decompression group).

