## 1. INTRODUCTION AND RATIONALE

### - Ménière's disease

Ménière's disease (MD) is an incapacitating disease of recurrent vertigo attacks, accompanied by hearing loss, tinnitus and/or aural fullness. Between the attacks of vertigo intervals of days, weeks or even months may occur (Lopez 2015, Pullens 2013). The natural course of MD has been studied and it has been found that the attacks of vertigo become less severe and disappear after two years in 60% and after eight years in 80% of patients (Portmann 1980; Silverstein 1989, Perez 2008, Van Esch 2016). In the end phase of the disease patients without vertigo attacks may still suffer from lasting hearing loss and tinnitus and chronic instability caused by hypofunction of the labyrinth. Significant comorbidity is seen in patients with Ménière's disease. The most important comorbidities that may also cause dizziness are anxiety disorders and BPPV (van Esch, 2016).

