#### 4.4 Sample size calculation

The sample size for this RCT was computed using software package PASS 11. The sample size calculation is based on the study performed by Saliba (Saliba 2015), in which complete control of vertigo was reached in 96,5% of the patients who underwent EDB. According to literature, endolymphatic sac decompression is effective in  $\pm 70\%$  of the patients (Brinson 2007, Convert 2006, Durland 2006).

We compare MD participants undergoing an operation with clip (EDB group: A group) independently with MD participants undergoing operation without clip (decompression group: B group). Null hypothesis is that the percentage points difference between groups is nil ( $p_A = p_B$ ), with two-sided alternative hypothesis ( $p_A \neq p_B$ ) and with anticipated 25% percent difference ( $p_A = 95\%$  and  $p_B = 70\%$ ). Power is at least 80%. The chance of a false positive finding for either of the analyses is controlled at the 5% level (family wise error rate). To obtain a power of at least 80% for Fisher's Exact test, the required sample size is 32 in groups A and B (allocation ratio = 1). Loss to follow-up will likely occur in a small percentage of cases ( $n=5$  per arm). No selective loss to follow-up is anticipated and a missing-at-random assumption seems reasonable. Missing outcomes will therefore be imputed using multiple imputation in the main analysis. Two sensitivity analyses will be conducted as well, where missing outcomes will be treated as failures or success, respectively. In this case the sample size would be 37 in group A and B (allocation ratio = 1). The total number of participants would be 74.

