## **8.2 Randomisation, blinding and treatment allocation**

### **8.2.1 Process of randomisation**

Participants will be allocated in the EDB group or endolymphatic sac decompression group using an automated telephone randomised service provided by Castor. Participants will be stratified according to gender and duration of MD (recent-onset versus mature MD participants). A “recent-onset MD participant” is defined as having their first MD vertigo attack in the last two years prior to inclusion. “Mature MD participants” have had their first MD vertigo attack more than two years prior to inclusion. By stratification for the duration of the disease, the effect of the natural course of disease on the outcome is reduced.

The two ear surgeons will be present up to wherein the sac is completely skeletonized. Then one of the surgeons will leave the OR. The randomisation for clip or decompression

operation will be performed using the automated telephone randomised service. The surgeon who leaves the OR will take care of the follow up and does not know whether the clip has been placed or not.

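### Randomisation is stratified by gender and disease duration but the primary test is unstratified: mildly conservative, and 0 to 2 points less powerful, if the strata are prognostic

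*Protocol*

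**What the plan says.** Section 8.2.1 of the protocol sets the strata: "Participants will be stratified according to gender and duration of MD". Duration is split at two years from the first attack, so there are four cells. The reason is given for duration only: "By stratification for the duration of the disease, the effect of the natural course of disease on the outcome is reduced". The introduction describes that natural course: attacks "disappear after two years in 60% and after eight years in 80% of patients".

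Section 10.1 fixes the primary test: "A chi-square test (or Fisher's exact test) will be performed on the primary outcome variable data". It adds "Any statistical tests will be two-sided" and asks for 95% limits where they can be estimated. Section 4.4 sizes the trial on an unstratified test too: "To obtain a power of at least 80% for Fisher's Exact test, the required sample size is 32 in groups A and B". Neither section 10 nor section 12.6.1 mentions the strata. The protocol itself chooses the primary test, so this is not a detail left open for a statistical analysis plan.

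**The concern.** When allocation is balanced within strata that predict the outcome, differences between strata largely stop contributing to the treatment difference. A plain 2x2 test still counts them in its variance. Its standard error is then too large, the true type I error sits below the nominal 5%, and some power is lost. The protocol takes the trouble to balance on duration because it expects duration to matter, then does not use that balance in the analysis. At stake is a little efficiency in a trial of 74, together with a primary effect estimate that matches the design.

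**Working it through.** **The plan's own figure.** With 95% against 70% and a two-sided 5% level, exact enumeration of two binomials gives Fisher's test 68.0% power at 32 per arm and 77.6% at 37 per arm. It first passes 80% at 39 per arm (80.7%). The figure of 32 fits the uncorrected chi-square, whose exact power there is 80.6%. That mismatch is a separate sample size matter, but it shows how much depends on which test section 10.1 finally means.

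**Inputs.** From the documents: 74 participants, 1:1 allocation, 95% against 70%, two-sided 5%, four strata, up to 1.3 women per man (1.3/2.3 = 56.5%). Assumed, because the documents give nothing: permuted blocks of 4, a 40/60 split on duration, and the stratum effects on the log-odds scale.

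**Type I error by formula.** Let p be the overall attack-free rate and p_k the rate in stratum k with share w_k. The unadjusted test uses p(1 − p). With balance within strata, the relevant variance is p(1 − p) − V, where V = Σ w_k (p_k − p)². Put R = V / [p(1 − p)]. The true two-sided error is then about 2[1 − Φ(1.96 / √(1 − R))]. Take p = 0.70, so p(1 − p) = 0.21, and shares 0.228, 0.342, 0.172, 0.258.

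- Duration log-odds 1.0, gender 0.3: rates 0.542, 0.763, 0.615, 0.813; V = 0.0116; R = 0.055; 1.96/√0.945 = 2.016; error 4.4%.
- Duration 2.0, gender 0.5: rates 0.407, 0.835, 0.531, 0.893; V = 0.0404; R = 0.192; 1.96/√0.808 = 2.181; error 2.9%.
- No stratum effect: V = 0; error 5.0%.

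**Simulation.** 74 participants, 6,000 trials per setting. CMH is the Cochran-Mantel-Haenszel test without continuity correction.

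| Log-odds, duration / gender | Power, Pearson | Power, CMH | Type I error, Pearson | Type I error, CMH |
|---|---|---|---|---|
| 0 / 0 | 86.4% | 86.1% | 5.2% | 5.2% |
| 1.0 / 0 | 86.2% | 86.5% | 4.2% | 4.8% |
| 1.5 / 0.4 | 86.4% | 87.8% | 3.7% | 4.9% |
| 2.0 / 0.5 | 86.8% | 88.9% | 3.2% | 5.1% |

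The Monte Carlo standard error of one power figure is √(0.86 × 0.14 / 6000) = 0.45 points, so the first two rows show no clear difference. The largest gain is 88.9 − 86.8 = 2.1 points. The type I errors agree with the formula. If only 64 participants were analysed, the gap would reach about 2.5 to 3 points under the strongest assumptions.

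**Separating Fisher's discreteness.** In the same settings Fisher's test has 80 to 81% power, and its error falls from 3.4% to 2.2%. With no stratum effect at all it is already about 6 points below Pearson, and that part has nothing to do with the strata. The like-for-like comparison is Fisher against a stratified exact test: 79.7% v 80.7% with non-prognostic strata, and 81.6% v 84.5% with odds ratios of 3 for gender and 5 for duration. That is a gain of about 1 to 3 points. (The simulated Fisher power exceeds the exact 77.6% because arm sizes vary slightly around 37, which makes the test less discrete.)

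**Sparseness and the form of the test.** Expected failures are 37 × 0.05 + 37 × 0.30 = 1.85 + 11.1, or about 13 in 74, spread over four strata. With so few events a continuity correction is costly: a corrected CMH has only about 75 to 80% power at 74 participants, below the Pearson test that section 10.1 already allows.

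**The case against.** The strongest reply is that nothing here is invalid. An unadjusted test under stratified allocation errs on the safe side and belongs to the same family as the test in the sample size. The loss also depends wholly on how prognostic the strata are. The documents give no effect size for duration and no evidence that gender matters. All of this stands, and it limits the point to efficiency.

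A reader might infer more, in four ways that the documents do not support:

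- That the 60% and 80% remission figures show a strong stratum effect. They describe the natural course of the disease, not attack-free rates 12 months after surgery by duration. Section 4.2 also admits only patients with more than 3 attacks in the past 6 months and at least 1 in the past 2, so those already in remission are left out.
- That ignoring the strata costs 6 to 9 points of power, by setting Fisher against CMH. Most of that gap is discreteness.
- That the trial has no power to spare. With Pearson's test, 74 participants give about 86% against a target of at least 80%. Fisher's shortfall is a sample size matter.
- That the change has no downside. The strata are sparse, and the wrong variant of the test would lose more than it gains.

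**Conclusion.** The mismatch between design and analysis is real and is fixed in the protocol's text. Its consequence is conditional and small. If the strata are prognostic, the planned chi-square test is mildly conservative (type I error from about 5% down to about 3%) and loses about 0 to 2 points of power at 74 participants, over assumed duration log-odds of 0 to 2.0 with gender log-odds up to 0.5. If they are not prognostic, nothing is lost. The direction follows from the protocol's own premise about duration; the size rests on assumed stratum effects, blocks of 4 and a 40/60 duration split. This is a cheap improvement, minor in size, and no threat to the trial's validity.

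**What to change.** In section 10.1, replace the open choice of tests with one primary test: Cochran-Mantel-Haenszel without continuity correction, over the four gender by duration strata used at randomisation. Report the Mantel-Haenszel common risk difference with its 95% confidence interval as the primary estimate, and keep the unadjusted 2x2 table as support. Say explicitly that the continuity-corrected version is not to be used. Add a line in section 4.4 so that the sample size text refers to the same test.

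The cost is a short amendment before unblinding. Both factors are already recorded, and no participant is added. A small cost remains: sparse strata contribute little information. How results are combined over imputed data sets has to be stated whichever test is used. That, and covariates in the secondary models, can be left to the statistical analysis plan.

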#### 10.1.1 Imputation of App-recorded data

The daily questionnaire taken via the DizzyQuest app is likely to contain missing data. All other missing data will be labelled 'NAmissing' in SPSS. Multiple imputation will be used to create complete data sets. Depending on the missing data pattern different strategies will be followed.

Imputation variables are base line measurements, time-course measurements and daily App-data.

- Missingness  $\leq 10\%$

If little data is missing, the data will be treated as one data-row per patient (wide format).

In this case, information for imputing missing values will be taken from the exact same time points of other patients. This strategy can account for possible time trends.

- Missingness  $> 10\%, \leq 50\%$

If more data is missing, the data of each patient will be split into one row per day (long format), when the previous 10 days will be included in each row. After imputation, the previous days will be removed to avoid duplication of data. This strategy includes information on missing data across time periods and can lead to wrong imputations for time trends longer than 10 days.

- Missingness  $> 50\%$

The same strategy as for missingness between 10% and 50% is followed except for including a smaller time window. 10 previous days will be used. If all primary outcome data are not available (missing), the participant will be excluded from the analyses. The a priori sample size estimation has been corrected for this.

The above cut-offs and time ranges reflect expectations. Actual values will be selected based on the variability of imputed values.

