### 4.2 Inclusion criteria

In order to be eligible to participate in this study, a patient must meet all of the following criteria:

- Definite unilateral MD according to diagnostic criteria of the Bárány Society (Lopez-Escamez, 2016)
- More than 3 patient reported attacks in the 6 months prior to inclusion and at least 1 attack in the 2 months prior to inclusion
- Age  $\geq$  18 years at the start of the trial
- Non responding to a sufficient extent to conservative medical treatment including at least two sessions of at least one intra-tympanic injection (IT) each with corticosteroids (dexamethasone, methylprednisolone, triamcinolonacetonide)
- Dutch health care insurance

Definite MD according to Bárány Society:

- Two or more spontaneous episodes of vertigo, each lasting 20 minutes to 12 hours,

AND

- Audiometrically documented low- to medium-frequency sensorineural hearing loss\* in one ear, defining the affected ear on at least one occasion before, during or after one of the episodes of vertigo,

AND

- Fluctuating aural symptoms (hearing, tinnitus, or fullness) in affected ear (not better accounted for by another vestibular diagnosis).

\*Low frequency sensorineural hearing loss is defined as increases in pure tone thresholds for bone-conducted sound that are higher (i.e. worse) in the affected ear than the contralateral ear by at least 30 dB HL at each of two contiguous frequencies below 2000 Hz

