|                      | Rinne left            | Positive
Negative                                             |
|                      | Dix Hallpike          | Positive
Negative                                             |
|                      | If positive: side:    | Left
Right                                                    |
|                      | Diadochokinesis       | Normal
Abnormal                                               |
|                      | If abnormal: side     | Left
Right                                                    |
|                      | Eye pursuit movements | Smooth
Abnormal                                               |
|                      | If abnormal: direct   | Left
Right
Up
Down                                      |

An MRI- and CT-scan will be performed and the patient is referred to a vestibular therapist. A PTA, vHIT and calorigram will be performed. Moreover, from the moment of inclusion, the patients starts reporting in de DizzyQuest App. This is a daily questionnaire of 31 questions addressing general functioning. In case of an attack, a short questionnaire is to be filled out. The inclusion and exclusion criteria will be double-checked by the coordinating investigator and if the patient does meet the criteria, the first survey package is sent through email. This survey pack consists of the HADS, DHI, THI, SF-36, EQ-5D VAS, NPQ, VADL, VAP and a questionnaire about expectations of the treatment.

All the pre-operative data is entered in Castor.

 The VAP and VADL are newly developed questionnaires to assess the effect of dizziness and/or balance problems on patients' ability to do things. They are not an outcome measure in this study, but we aim to anticipate on the possibility that the Bárány Society takes the outcomes of questionnaires into account in future studies. These questionnaires are taken for this trial as well, to enable comparison of the results of this study in the future that only use the VAP and the VADL.

In the following weeks, the patient visits the vestibular therapist, who takes the medical history and performs the first measurements. The patient is seen by the anaesthetist for regular pre-operative screening.

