#### **10.1.2 Computation of outcome**

The outcome will be determined from the imputed App-data. It is expected that attacks are reported reliably and missing data can be reliably imputed as being attack free. In principle, a patient can be sometimes imputed as having an attack on otherwise as being attack-free. To account for these potential cases, a cut-off of 10% for the attack probability (as the imputed frequency for having an attack) will be used to determine presence/absence of attacks.

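### Above 10% missing app data, the row-per-day imputation states no time since surgery and no pre/post-operative split, so imputed month-12 attack probabilities can be biased upward in both arms

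*Protocol*

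**What the plan says.** Protocol 10.1.1 sets three tiers by the amount of missing app data. At 10% or less the data stay wide, gaps are filled from other patients at the same time point, and the section says this copes with time trends. Above 10% and up to 50%, "the data of each patient will be split into one row per day (long format"), each row carrying the previous 10 days. The section adds that this "can lead to wrong imputations for time trends longer than 10 days". Above 50% the same strategy applies; a smaller window is announced, but the figure given is again 10 days.

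The imputation variables are baseline measurements, time-course measurements (not defined) and daily app data. Days since surgery is not named, and nothing separates rows before the operation from rows after it. The section calls its cut-offs and time ranges provisional.

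On what the app record contains, 8.3.1 says that "from the moment of inclusion, the patients starts reporting in de DizzyQuest App". Section 4.2 requires "More than 3 patient reported attacks in the 6 months prior to inclusion". On use, 10.1.2 says "The outcome will be determined from the imputed App-data", expects missing days to be imputed as attack-free, and applies a 10% cut-off to the imputed attack frequency without saying whether that is per day or per patient.

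**The concern.** The trial is designed to produce a trend far longer than 10 days: from at least four attacks in six months before surgery to none at month 12. Section 4.4 anticipates this result in 95% of one arm and 70% of the other. A missing month-12 day following 10 clean days looks, to a model with only a 10-day lag, much like a clean stretch between attacks before surgery. Its imputed attack probability is then averaged over periods when disease was active.

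Adding treatment arm or the patient's own overall attack rate does not cure this, because a responder's own pre-operative attacks then feed the month-12 imputation. At stake is the accuracy of the 12-month attack-free rates and, to a lesser degree, the contrast between arms.

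**Working it through.** The protocol gives no figure for imputation error, so there is none to reproduce. The check uses its design values where they exist and labels the rest as assumptions.

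**From the protocol:** 37 per arm and 95% v 70% success (4.4); more than 3 attacks in 6 months, so at least 4/182 = 0.022 per day (4.2); reporting from inclusion (8.3.1); 10-day lag (10.1.1); 10% cut-off (10.1.2).

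**Step 1: when does a clean patient cross 10%?** With m missing days and imputed daily probability p, the chance of any imputed attack is 1 − (1 − p)^m. It exceeds 10% when p > 1 − 0.9^(1/m).
- m = 6: 0.0174
- m = 9: 0.0116
- m = 15: 0.0070

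**Step 2: a 30-day window.** Assumed: 60 pre-operative days, a 30-day month-12 window, days missing at random, and cure either immediate or fading in over 90 days. Logistic imputation on the 10-day attack count, 20 imputations, 30 simulated trials per scenario. Each cell gives no time term / post-operative rows only / pre-post indicator plus day since surgery.

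| Attack rate per day | Missing | Cure | Imputed p on a missing day after 10 clean days | Cured classed as failures, per-patient cut-off |
|---|---|---|---|---|
| 0.022 | 20% | immediate | 0.006 / 0.004 / 0.004 | 4% / 1% / 2% |
| 0.022 | 20% | fading | 0.008 / 0.005 / 0.002 | 6% / 4% / 0.6% |
| 0.022 | 50% | immediate | 0.006 / 0.004 / 0.004 | 22% / 9% / 13% |
| 0.022 | 50% | fading | 0.008 / 0.006 / 0.002 | 37% / 24% / 4% |
| 0.044 | 20% | immediate | 0.010 / 0.006 / 0.008 | 11% / 5% / 8% |
| 0.044 | 20% | fading | 0.014 / 0.010 / 0.004 | 22% / 13% / 3% |
| 0.044 | 50% | immediate | 0.010 / 0.007 / 0.008 | 57% / 28% / 43% |
| 0.044 | 50% | fading | 0.015 / 0.011 / 0.004 | 78% / 56% / 16% |

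Restricting to post-operative rows helps more when cure is immediate, and the time term helps more when it fades in. Under a per-day cut-off the last column is 0% in every scenario for all three models.

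**Step 3: a 90-day window.** Assumed: 60-day run-in, fading over about 2 months, 15% missing, predictors limited to the 10-day count and baseline frequency, 80 trials. The true month-12 probability is 0.0042 per day. Imputed: 0.0115 without time, 0.0119 after adding arm and own rate, and 0.0039 from post-operative rows with time since surgery. With a per-patient cut-off, 66% of attack-free patients are misclassified without time and 7% with it.

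**Step 4: the contrast between arms.**
- 90-day window, averaging over imputations with no cut-off, 15% missing: 82 − 62 = 20 points without time, 91 − 68 = 23 with. At 30% missing: 72 − 55 = 17 and 87 − 67 = 20. The cost is about 3 points.
- 30-day window, also averaged: adding time changes the difference by −0.5 to +2.3 points (for example 76.9 − 66.4 = 10.5 against 92.0 − 79.4 = 12.6). With 30 × 37 = 1,110 patients per arm, one rate near 85% has a simulation standard error of √(0.85 × 0.15 / 1,110) = 1.1 points, so these changes are close to noise.
- Harshest 30-day scenario, per-patient cut-off: 22% v 17% without time and 83% v 72% with it, against a true 96% v 76%.

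**The case against.** A reader might infer that cured patients will become failures, in the order of two-thirds of them. The documents do not support that. The 66% rests on a 90-day window the protocol never states, on a per-patient reading of the cut-off, and on a model that omits predictors 10.1.1 lists. Sections 8.3.1 and 8.3.3 supply a 31-item daily questionnaire and visit scores at 3, 6 and 12 months, which can partly separate active from resolved disease. Repeating the 90-day simulation with one noisy visit score (assumed separation about 1.7 SD) cut 66% to 26%; the model with time gave 7.5%. Over 30 days with 15% missing the figure is about 3%: at 0.0115 per day, 10 missing days are needed to pass 10%, and 30 × 0.15 = 4.5 are expected. This objection stands against the size, not the direction.

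A reader might also infer that the plan excludes time since surgery. It does not; it is silent, and the undefined time-course measurements or an analysis plan could supply it. Nor does the conceded limitation prove its absence, since patient-specific trends longer than 10 days can survive a common time term. What remains is that the protocol fixes a method, states only a short lag, and admits the resulting error on the kind of trend its endpoint measures. Calling cut-offs and time ranges provisional does not add a time term or separate the periods.

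Scope and mitigation also count. The issue arises only above 10% missingness, 12.1 has missed questionnaires detected nightly and chased, and attacks have their own short form.

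**Conclusion.** The point holds in limited form. Above 10% missingness the stated method can bias month-12 attack probabilities upward in both arms, roughly 0.006 to 0.015 per missing day against 0.002 to 0.008 with a time term in the 30-day scenarios. Under a per-patient cut-off this classed 4% to 78% of cured patients as failures without time, against 0.6% to 43% with a pre/post indicator and day since surgery. Under a per-day cut-off it was nil. The arm difference shrinks modestly: about 3 points at most on averaged rates, more only in harsh per-patient scenarios.

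All sizes rest on assumed missing fractions, attack rates, windows, speeds of cure and a reduced predictor set. The missing time term is not the only cause. With 90 days and 30% missing, the model with time still misclassified about 46%, because the 10% cut-off is low and cured patients are pooled with uncured ones.

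**What to change.** In both long-format tiers of 10.1.1:
1. Impute post-operative days from post-operative rows only, with pre-operative attack frequency as a baseline covariate.
2. Add days since surgery (or visit interval) as a predictor in every row.
3. Then revise the caveat on longer trends to describe the changed method. Deleting it alone would remove a disclosure and correct nothing.

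It is worth stating the unit of the 10% cut-off in 10.1.2 at the same time, since that decides whether the bias reaches the endpoint. The change needs wording and a few lines of imputation code, with no new data and no patient burden. It should be settled before unblinding, because imputation predictors chosen afterwards would be open to challenge.

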#### **8.6 Follow-up of subjects withdrawn from treatment**

A participant may be excluded from the study prior to the expected protocol completion for safety reasons, failure of subject to adhere to protocol requirements, or subject consent withdrawal. Since early withdrawal could be related to the surgery, it is of great importance to analyse these final data for the integrity of the study. If a participant withdraws consent to continue follow up participation, attempts should be made to obtain permission to record at least primary outcome data. The participant will be contacted by phone and email, the next-of-kin will be contacted, a letter asking to contact us will be send or the patient's general practitioner will be contacted.

If a participants withdraws its consent, he/she is allowed to do so without further explanation. If this is the case, participants should contact the ENT-surgeon who takes care of follow up. This ENT-surgeon then contacts the coordinating researcher. The data that were collected until the moment of consent withdrawal, will be used in the analyses.

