#### **12.6.1 Data analysis and release of results**

The data from the trial will be centrally analysed from Participating Centres by the trial statistician.

We plan to use non-parametric tests in the analysis of the data. Non-parametric methods are more robust as they make fewer assumptions (distribution of the data). As a downside non-parametric are less efficient, i.e. they need a higher sample size to achieve the same power. As a compensating factor we use the relative efficiency of the Mann-Whitney U-test as compared to the t-test which has been estimated as 95% (Conover 1999, Practical Nonparametric Statistics).

In order to estimate a realistic treatment effect that avoids bias due to treatment-arm crossover and selective drop-out, an intention-to-treat analysis will be conducted as the primary analysis.

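### Sections 4.4 and 10.1.1 give incompatible rules for a randomised participant with no primary outcome data: one imputes the outcome, the other excludes the participant, against the stated intention-to-treat analysis

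*Protocol*

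**What the plan says.** Protocol section 4.4 assumes data missing at random and states: "Missing outcomes will therefore be imputed using multiple imputation in the main analysis". It adds two sensitivity analyses, one counting missing outcomes as failures and one as successes. It raises the sample from 32 to 37 per arm for five losses per arm.

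Section 10.1.1 imputes app data by three strategies according to the amount missing, the last of them for more than 50% missing. Under that last heading it says: "If all primary outcome data are not available (missing), the participant will be excluded from the analyses". The next sentence says that the sample size estimate was corrected for this.

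Section 10 opens with: "All analyses will be performed through Intention to treat". Section 10.1 repeats this for the primary outcome. Section 12.6.1 gives the reason, which is to estimate an effect that "avoids bias due to treatment-arm crossover and selective drop-out, an intention-to-treat analysis will be conducted as the primary analysis".

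Section 8.6, on withdrawn participants, says: "Since early withdrawal could be related to the surgery, it is of great importance to analyse these final data". It also asks staff to seek permission to record at least the primary outcome, and keeps the data collected before withdrawal.

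**The concern.** Two rules in the current text govern the same person. Under 4.4 a randomised participant with no primary outcome data is imputed in the main analysis and appears in both sensitivity analyses. Under 10.1.1 that person is in none of them, because the exclusion is from the analyses generally and not only from the primary one. No other section reconciles the two.

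The sample-size sentence adds to the conflict. The only correction in 4.4 is the five per arm for loss to follow-up, and 4.4 says the outcomes of those five are imputed. The same allowance is therefore tied to two different treatments of the data.

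Removing people because of something that happened after randomisation is not an intention-to-treat analysis. Section 12.6.1 relies on intention to treat to guard against selective drop-out, and 8.6 accepts that early withdrawal may be related to surgery. If the choice of rule is still open when results are seen, it can be made with knowledge of which rule favours which answer.

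**Working it through.** **Inputs**
- Required number per arm: 32; added for loss: 5; randomised: 37 per arm, 74 in total (4.4).
- Two-sided testing: "Any statistical tests will be two-sided" (10.1), at the 5% level.
- Test: Fisher's exact test in the sample size (4.4); chi-square or Fisher's in the analysis (10.1).
- Assumed for illustration, not from the protocol: attack-free completers 30/32 in the EDB arm and 22/32 in the decompression arm, with five missing per arm. The 25-point gap matches the planned difference.

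**The plan's allowance.** 32 + 5 = 37 per arm and 2 × 37 = 74, as stated. The loss is 5/37 = 13.5%. Whether 32 per arm gives the stated power is a separate question on which nothing here depends.

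**How many are affected.** The phrase in 10.1.1 about all primary outcome data is not defined.
- Wide reading (no 12-month outcome): everyone lost without a retrieved 12-month status is excluded. At the planned loss this is up to 2 × 5 = 10 of 74, or 13.5%. Section 8.5 speaks of at least 15% drop-out; 0.15 × 74 = 11.1, about 11.
- Narrow reading (no postoperative app data at all): only people who reported nothing are excluded. Partial reporters, even above 50% missing, are imputed.

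**What each treatment gives.** Difference = a/n(EDB) − b/n(decompression), with two-sided Fisher p-values.

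| Treatment of the five missing per arm | EDB | Decompression | Difference | p |
|---|---|---|---|---|
| Excluded (10.1.1) | 30/32 | 22/32 | 25.0 points | 0.022 |
| All failures (4.4 sensitivity) | 30/37 | 22/37 | 21.6 points | 0.074 |
| All successes (4.4 sensitivity) | 35/37 | 27/37 | 21.6 points | 0.024 |
| EDB failures, decompression successes | 30/37 | 27/37 | 8.1 points | 0.58 |
| EDB successes, decompression failures | 35/37 | 22/37 | 35.1 points | 0.0006 |

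The first two rows fall on opposite sides of 5% with Fisher's test. The last two rows are in neither section.

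**Dependence on the test.** With the uncorrected chi-square test, the all-failures row gives a pooled proportion of 52/74 = 0.703 and z = 0.2162/√(0.703 × 0.297 × 2/37) = 2.03, p = 0.042. The excluded row gives 52/64 = 0.8125 and z = 0.25/√(0.8125 × 0.1875 × 2/32) = 2.56, p = 0.010. In this example the change of side occurs with Fisher's test and not with the uncorrected chi-square.

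**Where imputation would land.** If imputation used arm only, the average imputed result would be (30 + 5 × 30/32)/37 − (22 + 5 × 22/32)/37 = 0.9375 − 0.6875 = 25.0 points, the excluded-set figure. For participants with little data, the visible gap between the two rules is thus in the sensitivity analyses more than in the main estimate.

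**The case against.** The strongest reply is that the exclusion is narrow and the protocol works to keep it rare. It applies only when the primary outcome data are wholly missing, and 10.1.1 imputes everyone else. Section 8.6 keeps data up to withdrawal and sends staff after the primary outcome by phone, email, letter, next of kin or general practitioner. Section 12.1 has app use monitored every night and missed entries followed up. Section 4.3 excludes people unable or unwilling to use the app. All of this stands, so ten exclusions is an upper-end case for the planned loss.

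A reader might infer that every early withdrawal leaves the primary comparison, or that the trial has a complete-case analysis. The documents do not support either: someone who reports for some weeks and then stops is imputed on the narrow reading, and multiple imputation is the general method.

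A reader might also infer that restoring these participants would remove bias from informative loss. It would not. Suppose the true counts are 35/37 v 26/37 (24.3 points), and the five lost are all successes in the EDB arm and all failures in the decompression arm. Exclusion gives 30/32 v 26/32, 12.5 points (p = 0.26). The two 4.4 sensitivity analyses give 30/37 v 26/37 (p = 0.42) and 35/37 v 31/37 (p = 0.26), both 10.8 points and no closer to 24.3. Imputation under missing at random would also stay near the excluded-set figure.

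None of this reconciles the two rules. Section 4.4 makes no exception for wholly missing outcomes, and sections 10, 10.1 and 12.6.1 make none to intention to treat.

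**Conclusion.** The contradiction is in the current text and should be removed. Section 10.1.1 excludes participants whom 4.4 imputes, and the exclusion does not fit the stated intention-to-treat analysis. Read literally, it also takes out of the 4.4 sensitivity analyses some of the participants they were written for.

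The number affected is unknown, and is about 10 of 74 if the planned losses all fall under the rule. In the illustration, exclusion reports 25.0 points with p = 0.022, while retaining the missing as failures reports 21.6 points with p = 0.074. This rests on assumed completer counts, five wholly missing per arm and Fisher's test. It shows that the rule can matter to significance. It does not predict the direction or size of any bias, which the documents cannot settle.

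**What to change.** In section 10.1.1, delete the exclusion sentence and the sentence saying that the sample size was corrected for it. Then state the following:

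- All 74 randomised participants are in the primary analysis. A wholly missing 12-month outcome is multiply imputed as in 4.4, from arm, stratification factors, baseline attack frequency and any available follow-up data.
- The same participants are in both 4.4 sensitivity analyses.
- Primary outcome data count as missing under a written definition that separates no 12-month outcome from no postoperative app data.
- The excluded-set result, if wanted, is supplementary only.
- Two further sensitivity analyses set missing outcomes in opposite directions: EDB failure with decompression success, and the reverse. These are needed because imputation under missing at random, and analyses that set both arms the same way, neither correct nor fully expose loss that depends on outcome differently by arm.

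The cost is protocol or SAP wording, a little more analysis and slightly wider intervals, with no new data. For participants with baseline data only, imputation adds little information. The change should be settled before unblinding.
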